### Sample size

Our sample size estimation is based upon our primary outcome (see Objective 2), which is live-birth rates between randomized groups at the CHUS. Based on the Fertility Fitness Program, the inclusion of 58 women per group will provide our study a power of 80 % to identify a doubling in live-birth rates with our program (25 to 50 %, α = 5 %). Assuming a dropout rate of 10 % (these women are usually highly motivated), our final estimated sample size will be 128 women. For other objectives and outcomes, it would be difficult to assess power because similar evaluations have not been previously reported.

### Knowledge translation and transfer plan (Objective 4)

It is worth mentioning that both our research program and research design are optimal to allow knowledge translation (KT) and application throughout the entire research process. Integrated KT is an important outcome of this research and will take form of regular meetings of the Advisory and Steering committees. Because of the involvement on these committees of representatives of Quebec and Ontario Ministries of Health, fertility clinics and CON, as well as expert clinicians, diffusion of results and exchange of experiences will be facilitated.

However, research by itself does little to induce change (except for participants) and thus, results have to be diffused to interested audiences. Our research is relevant to health professionals, healthcare system decision-makers and policy-makers, patients and Canadian population. We will reach out to these target audiences through linkage and exchange activities, including presentation of study results at local, national and international scientific meetings attended by interested stakeholders in the obesity, reproductive endocrinology, fertility and health services fields and publication in scientific journals, but also by direct reports to healthcare system decision-makers. A clear summary of research results, including key messages targeted for each selected audience and synthesized results, will be available (printed and on a web site). Local and national media will be invited to press conferences and we will schedule private meetings with important decision-makers to whom our findings are relevant.

## Discussion

This paper has outlined the protocol of a study assessing clinical outcomes and costs of a transferable interdisciplinary lifestyle intervention, before and during pregnancy, in obese infertile women. We are using a RCT design for proximal clinical outcomes, and mixed design for cost-effectiveness evaluation and qualitative assessment for the purpose of future dissemination and knowledge transfer. To our knowledge, we are the first in the world to conduct such a program with lifestyle intervention continuing throughout fertility treatments and pregnancy. This project is very important as it will generate new knowledge about the implementation, impacts and costs of a lifestyle management program in obese infertile women. The results of this study will provide valuable information on feasibility and transferability of such a program, including identification of barriers and solutions. We expect that our program will improve the lifestyle and fertility of the participants and reduce maternal and fetal complications during pregnancy, as compared with our different control groups. A significant reduction in cost per live birth and cost-effectiveness ratio is also anticipated.

Although this research protocol is innovative and uses a robust methodology, some limitations need to be acknowledged. First, implementation and outcome evaluation of the lifestyle program will take place in a single clinic. However, a RCT at the CHUS will be performed with sufficient power to assess the primary outcome. Results will also be compared to three other clinics, which is an ideal first step for the future development of a multicenter RCT. It is important to appropriately design and evaluate the program in one center before transferring it to other centers. Second, some of the outcome measures will be self-reported and might be biased. However, such bias should be similar in both randomized groups and the results will be triangulated with data from many different sources (administrative data, questionnaires, focus groups, etc.). Third, most of the outcomes will be assessed only retrospectively in the clinics of comparison. This might introduce an evaluation bias although multiple sources of information will be used and compared. A recall bias is also possible for the evaluation of costs for the patients’ viewpoint in these clinics, but the same estimations will be performed in Sherbrooke and compared with real costs, which will allow the determination of the degree of this bias for comparison clinics. Fourth, in Sherbrooke, fertility treatments, including IVF, will be covered by the public health care system. Therefore, some results may not reflect all North American fertility clinics, but the same results will be compared to clinics in other provinces where fertility treatments are not covered.

The outcome measures of this study will be relevant to a number of health systems’ managers and policy-makers. Indeed, new approaches aiming at increasing efficiency and reducing costs of fertility treatments, while improving care, are thus very pertinent for these policy-makers. This research proposal is completely in line with those objectives and is developed in partnership with local, provincial and national decision-makers, which increases the potential impact and use of the findings. Generalizability of our findings is increased by the evaluation of clinics from three different provinces and the involvement of the CON as a partner. Furthermore, experts and decision-makers from various provinces will participate on the Advisory committee to ensure that the developed intervention can be applied in other contexts. Early and active involvement of decision-makers will ensure that the intervention is appropriately designed to be implemented in most North American fertility clinics.

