### Randomisation

An independent statistician will use computerised random number generation to allocate each participant to the intervention or control group. Randomisation will be stratified according to the PCOS or non-PCOS status, based on clinical diagnosis in the patient’s record. Sequences will be generated using permuted block randomisation, with block sizes of two, four or six entries. The allocation sequence will be concealed in corresponding sequentially numbered opaque envelopes. After a participant has completed baseline assessments, the research coordinator will open the envelope to reveal the group allocation to the participant. Participants will be informed of their group assignment at that time.

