#### Intervention arm

Participants allocated to the intervention group will be invited to participate in the interdisciplinary lifestyle intervention and will have to delay other fertility treatments for six months. After 6 months of lifestyle intervention alone, women who are not pregnant will begin pharmacologic fertility treatments, as indicated, in conjunction with the lifestyle intervention that will continue to be offered. The aim of the intervention will be to implement progressive and sustainable lifestyle changes in order to reach a modest weight loss. Women will be invited to individually meet with a dietitian and a kinesiologist (20–30 min each) at 0, 3, 6 weeks and then every 6 weeks over a period of 18 months or until the end of pregnancy. A follow-up phone call/email will also take place once between each meeting for additional support. The dietitian will use 3-day food records to evaluate the women’s food intake throughout the program. To help improve patient’s diet, Canada’s Food Guide and the “Healthy Plate” [51] will be the main tools use for nutritional counselling. The kinesiologist will be responsible for taking anthropometric measures and vital signs and for coaching women to increase their physical activity level. A pedometer will be offered to assist the patient. Patients will be guided by the dietitian and the kinesiologist to formulate S.M.A.R.T goals (specific, measurable, attainable, realistic, and timely) at each meeting. The members of our interdisciplinary team will be trained in motivational interviewing. This training can positively affect the attitude to behaviour change in obese infertile women [52].

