##### Lifestyle:

Physical activity level and eating habits will be measured using a questionnaire adapted from the one used by Statistics Canada for the latest Canadian Health Survey. This questionnaire inquires about the frequency and duration of active travelling, leisure time, and sedentary activities (television watching, video games, computers). We chose this questionnaire since it allows comparison of the characteristics of our patients to those of the general Canadian population. Moreover, women will be asked to wear a tri-axial accelerometer (GT3X+, Actigraph, Pensacola, FL, USA) on their hip for seven consecutive days except during sleep and showering/bathing. The accelerometer will be used to estimate daily energy expenditure from physical activities, time spent in various physical activity intensities and step count. The GT3X+ has been shown to be a valid and reliable measure of physical activity in free living conditions [66].

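### The protocol says self-report bias should be similar in both arms, but its own design allows the bias to differ for the questionnaire outcomes, plausibly in favour of the intervention

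*Protocol article*

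**What the plan says.** Among its limitations, the Discussion admits that "some of the outcome measures will be self-reported and might be biased". It then offers two reassurances: "However, such bias should be similar in both randomized groups", and "the results will be triangulated with data from many different sources". The sources it names are administrative data, questionnaires and focus groups, followed by an open-ended etc.

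The following sections bear on the first reassurance:

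- **Randomisation.** The envelope is opened after the baseline assessments. "Participants will be informed of their group assignment at that time".
- **Intervention arm.** Women see a dietitian and a kinesiologist at 0, 3 and 6 weeks and then every 6 weeks for up to 18 months, with a call or email between meetings and goals set at each one. "The dietitian will use 3-day food records to evaluate" intake, and the kinesiologist is charged with "coaching women to increase their physical activity level". Table 1 adds 12 group sessions, with nutrition, exercise, sleep, alcohol and smoking among the topics.
- **Control arm.** Standard fertility treatment, which may include lifestyle counselling by the treating specialist.
- **Lifestyle.** "Physical activity level and eating habits will be measured using a questionnaire". Table 2 gives a questionnaire as the source for diet, exercise, sleep, alcohol and tobacco. A hip accelerometer worn for seven days separately gives energy expenditure, time by intensity and step count.

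**The concern.** Bias that is equal in two arms cancels in their comparison; bias that differs between arms does not. The Discussion relies on the first case and gives no reason for it. The women answering the follow-up questionnaires know their group, and those in one group have been taught, visit after visit, what the desirable answers are.

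Lifestyle change is a named category of secondary outcomes under Objective 2, and the Discussion expects the programme to improve participants' lifestyle. Results are to go directly to decision-makers. A between-arm difference on the questionnaire that reflects reporting could be presented as a change in behaviour, with the sentence in the Discussion cited as assurance that it is not.

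**Working it through.** **1. Can the bias differ between arms?** Three conditions matter, and the protocol settles each.

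- *Knowledge of allocation at the time of reporting.* Baseline answers are given before the envelope is opened; all later answers are given after it. Taking change from baseline therefore does not remove a shift that begins with the intervention.
- *Overlap between what is taught and what is asked.* Diet and activity are the subject of every individual meeting. Sleep, alcohol and smoking appear in the workshops (Table 1, sessions 6 and 9). The questionnaire covers the same five habits.
- *Contrast between arms.* The structured programme exists in one arm. In the other, counselling is optional and comes from the physician.

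So the bias can differ, and the likelier direction is towards the intervention. Randomisation balances women's tendencies at baseline, not an influence that starts after allocation.

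**2. Do the named sources remove it?** Questionnaires and focus groups are further self-report. Administrative data are independent of the woman's account, but as described they cover laboratory tests, hospitalisations and costs, not diet, sleep, alcohol or tobacco. The accelerometer can check physical activity, but the sentence on triangulation does not name it. The protocol describes no objective measure of the other four habits.

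**3. How large could the effect be?** The protocol gives no size for the bias, so the shift below is an assumption.

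*Sample size used.* The plan's 58 per group (live birth 25 % v 50 %, two-sided 5 %, power 80 %) reproduces:

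n = [1.960 × √(2 × 0.375 × 0.625) + 0.842 × √(0.25 × 0.75 + 0.50 × 0.50)]² / 0.25² = 57.7, rounded up to 58.

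That figure is unaffected by this point; it only supplies the n.

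*Model.* A continuous questionnaire score, no true change, and reports in the intervention arm shifted by d standard deviations. The test is the planned two-tailed unpaired t test with df = 2 × 58 − 2 = 114 and noncentrality d × √(58/2) = 5.385 d. The probability counted is that of a significant result in favour of the intervention.

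- Uncorrected α = 5 %: critical value 1.981.
- Bonferroni over five comparisons (the five named habits), α = 1 %: critical value 2.620.
- Bonferroni over ten comparisons, α = 0.5 %: critical value 2.863.

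| Assumed shift d (SD) | Noncentrality | α = 5 % | α = 1 % | α = 0.5 % |
|---|---|---|---|---|
| 0 | 0 | 2.5 % | 0.5 % | 0.25 % |
| 0.2 | 1.077 | 19 % | 6.5 % | 4 % |
| 0.3 | 1.616 | 36 % | 16 % | 11 % |
| 0.5 | 2.693 | 76 % | 53 % | 44 % |

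The no-bias comparator for a benefit is half of α, because only one direction is counted. Data analyses and interpretation plans Bonferroni correction but does not state the number of comparisons; five and ten are illustrations. Correction lowers the rates but leaves the bias in the estimate.

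**The case against.** The best case for the plan is that it is candid and guarded. The sentence stands in a list of limitations, says the outcomes might be biased, and says the bias should be similar, not that it will be. Controls may also be counselled, and women in both arms know they are in an obesity study and answer the same questions on weight, activity and readiness to change, so pressure to please is not absent among controls. Weight, body fat, blood markers, walk distance and accelerometer activity are measured rather than reported. The choice between two measures of activity could properly be left to an analysis plan that is not shown. The shifts used above are assumed, and a t test does not suit categorical items such as tobacco use, for which the protocol plans chi-square or Fisher's exact tests.

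Most of this stands and limits the point. It does not rescue the reassurance: the contrast in coaching is the purpose of the trial, and the measured outcomes verify activity at most among the five habits. The absence of a precedence rule is not the fault alleged here; the fault is a stated property that the design does not give.

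A reader might go further and infer three things that the documents do not support:

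- That the bias exists in one arm only and certainly favours the intervention. The protocol gives neither direction nor size, and practice with food records could also make coached women report more accurately.
- That the plan explicitly treats the questionnaire as unbiased between arms. It assumes similar bias, and nothing makes the questionnaire the deciding measure.
- That the main result is in doubt. Live birth is taken from medical records.

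**Conclusion.** The statement is wrong as written. With unblinded participants and structured coaching in one arm on the very behaviours being reported, bias in the questionnaire outcomes can differ between arms and plausibly favours the intervention. Neither randomisation nor the named triangulation sources remove it.

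The point is confined to self-reported secondary outcomes. The primary outcome, the sample size and the measured outcomes are not affected. The size is unknown: the tabulated rates hold only under an assumed shift in the intervention arm alone, a continuous score, 58 women analysed per arm and the stated number of comparisons. They show that a moderate shift would be enough to matter, not that one will occur.

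**What to change.** 1. In the Discussion, replace the sentence on similar bias with a statement that reporting bias may differ between the randomised groups and may favour the intervention, because participants know their group and only one group receives the structured programme.
2. Base the between-arm conclusion on physical activity on the accelerometer outcomes (steps, time by intensity, energy expenditure), with the questionnaire as supportive evidence. Comparison with the general Canadian population, which the protocol gives as its reason for choosing this questionnaire, can remain.
3. Interpret between-arm differences in self-reported diet, sleep, alcohol and tobacco as supportive or exploratory.

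A rule that admits a lifestyle claim only when weight or body fat moves the same way is not recommended. It would not validate reports of sleep, alcohol or tobacco, and it would misbehave in pregnant women, who are assessed again at 24–28 weeks, when weight gain is expected.

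The cost is small. The accelerometer data are already scheduled in both arms at baseline and every 6 months, so no new measurement is needed; the changes are to wording and to the standing of some secondary outcomes. The downside is weaker claims for self-reported habits.

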**Discussion:**

This study will generate new knowledge about the implementation, impacts and costs of a lifestyle management program in obese infertile women. This information will be relevant for decision-makers and health care professionals, and should be generalizable to North American fertility clinics.

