## Methods/Design

### Study design and setting

The proposed study relies on a participatory research approach which will combine quantitative and qualitative assessments. The impacts of the lifestyle program that will be developed will be assessed using a randomized controlled trial in one academic center. The study was registered to ClinicalTrials.gov (NCT01483612).

The RCT will be conducted at the CHUS fertility clinic, a fertility clinic with satellite access to IVF. The clinic offers care to patients with a range of reproductive problems including infertility, recurrent pregnancy loss, anovulation, PCOS, hyperprolactinemia, endometriosis, etc. The clinic has a successful ovulation induction and superovulation program including intrauterine insemination and access to donor sperm. Since 2011, it offers an IVF program in collaboration with Procrea Cliniques initially, and subsequently with the assisted reproduction center of the CHU Ste-Justine, where only the egg retrievals and embryo transfers are performed (evaluation of patients, protocol prescription, monitoring and decision making before and during cycles is done in Sherbrooke). Clinical outcomes and costs will be compared to a randomly assigned control group and to similar women seen in three fertility clinics across Canada not offering specific weight loss interdisciplinary lifestyle program: 1) an intra-provincial clinic (Procrea Cliniques, Montreal) with public coverage of fertility treatments; 2) 2 extra-provincial clinics (Centre for Fertility and Reproductive Health and IVF Unit at Mount Sinai Hospital, Toronto; and Fertility Clinic of Royal Alexandra Hospital, Edmonton) without public coverage of fertility treatments. These centers offer the full range of ART on site.

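### Comparison with clinics in uncovered provinces cannot show the programme's effect without public coverage, because none of those clinics offers the programme

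*Protocol article*

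**What the plan says.** **Where the programme runs.** The limitations paragraph of the Discussion says that "implementation and outcome evaluation of the lifestyle program will take place in a single clinic". It adds that "in Sherbrooke, fertility treatments, including IVF, will be covered by the public health care system", which applies to both randomised arms.

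**The external clinics.** Study design and setting describes them as "three fertility clinics across Canada not offering specific weight loss interdisciplinary lifestyle program". One is "an intra-provincial clinic (Procrea Cliniques, Montreal) with public coverage of fertility treatments". The other two, in Toronto and Edmonton, have no such coverage: "Royal Alexandra Hospital, Edmonton) without public coverage of fertility treatments". Their outcomes come from retrospective chart review and administrative data (Objective 2 outcomes section). Table 2 marks programme costs there as not applicable.

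**The response to the coverage limit.** The fourth limitation accepts that coverage may make some results unrepresentative of other North American clinics, and continues: "but the same results will be compared to clinics in other provinces where fertility treatments are not covered".

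**The wider claims.** The Abstract says that the information from the study "should be generalizable to North American fertility clinics". The last paragraph of the Discussion says: "Generalizability of our findings is increased by the evaluation of clinics from three different provinces", and it also cites the Canadian Obesity Network partnership.

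**The clinics as comparators.** Objective 2 (Study objectives) assesses the programme's impact against both the randomised controls and the external clinics. The opening of the Discussion expects benefit against all of these control groups. Data analyses and interpretation plans end-of-study comparisons across the two Sherbrooke groups and the three clinics.

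**The concern.** The limitation concerns whether the programme's effect would be the same where women pay for treatment. The comparison offered in response involves women who never receive the programme. It can show how usual care performs without coverage, but not what the programme would add there.

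Coverage could plausibly change the effect. According to the Control arm and Intervention arm sections, controls start standard fertility treatment once it is indicated, while intervention women postpone it for six months. The randomised contrast therefore depends on how readily women obtain standard treatment, and that may differ where they pay for it.

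Two conclusions are at stake. Policy-makers, a named audience, could take the results as evidence for settings that the trial cannot speak to. And because the objectives treat the external clinics as comparators for programme impact, a difference between the CHUS intervention arm and Toronto or Edmonton could be reported as programme benefit when part of it comes from coverage, centre or data source.

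**Working it through.** **1. The plan's own figure.** Sample size gives 58 women per group for live-birth rates of 25 % and 50 %, 80 % power and α = 5 %. A two-sided test of two proportions with pooled variance and no continuity correction gives 58 per group, with power 0.802. For dropout, 116 × 1.10 = 127.6, which rounds up to the stated 128. The randomised comparison is sized as claimed, and the point below does not depend on it.

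**2. Which combinations are observed** (Study design and setting; Discussion).

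| | Public coverage | No public coverage |
|---|---|---|
| Programme | CHUS intervention | none |
| No programme | CHUS control, Montreal | Toronto, Edmonton |

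**3. Estimability.** Write the expected outcome of a group as

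μ = a + b·P + c·C + d·P·C,

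where P = 1 with the programme and C = 1 with coverage. The rows (1, P, C, P·C) are:

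- CHUS intervention: (1, 1, 1, 1)
- CHUS control and Montreal: (1, 0, 1, 0)
- Toronto and Edmonton: (1, 0, 0, 0)

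There are three distinct, linearly independent rows for four parameters, so the rank is 3 of 4. In every row the second and fourth entries are equal, because the only group with the programme is covered. Any estimable combination must share that property.

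- Programme effect with coverage, b + d, is (0, 1, 0, 1): estimable, as CHUS intervention minus CHUS control.
- Programme effect without coverage, b, is (0, 1, 0, 0): not estimable.
- Change in effect with coverage, d, is (0, 0, 0, 1): not estimable.

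More women, or covariate adjustment within these groups, does not fill the empty combination.

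**4. What the cross-clinic contrast contains.** Let u be the usual-care live-birth rate, in per cent, in an uncovered clinic. The documents give no value for u. At the design rates,

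CHUS intervention − uncovered clinic = 50 − u = (50 − 25) + (25 − u).

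The first bracket is the programme effect under coverage, which the randomised arms already estimate. The second is the usual-care difference between CHUS and the uncovered clinic: coverage, centre, province, case mix, and prospective versus retrospective data. It may be positive or negative. The programme's effect without coverage appears in neither bracket.

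As an illustration, assume u = 10, 15 or 25. The contrast is 40, 35 or 25 points. Suppose the programme multiplied the uncovered rate by some ratio between 1 and 3. Its true effect there would be u × (ratio − 1): 0 to 20, 0 to 30 or 0 to 50 points. The observed contrast would be the same for every ratio, so the data could not tell these cases apart.

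**5. Costs.** Programme costs are collected only at CHUS (Table 2), and the cost-effectiveness section applies Quebec prices at every site. The economic comparison therefore has the same empty combination and does not use the other provinces' prices.

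**The case against.** The protocol is more careful than a quick reading suggests. It volunteers the coverage limitation, lists the single clinic as its first limitation, describes the external comparison as a step towards a multicentre randomised trial, and says that the programme should be evaluated in one centre before transfer. The Abstract's claim covers implementation and costs as well as clinical impact. The Discussion says that generalisability is increased, not established, and rests it also on the Canadian Obesity Network and the advisory committee. The planned analysis keeps the CHUS control arm beside the external clinics, Montreal supplies a second covered usual-care group, and multivariate adjustment is foreseen.

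Most of this stands, and it rules out two stronger readings. A reader might infer that the protocol claims the comparison cancels the coverage problem. It does not say so; it sets the comparison against the limitation without saying how far it helps. A reader might also infer that the trial yields nothing relevant to uncovered settings. That goes too far: Toronto and Edmonton will show usual-care outcomes, treatment use and patient experience there, and conceptions during the six-month lifestyle-only phase may depend less on coverage, although that phase has no untreated comparator.

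The gap remains. Neither the partnership nor the committee supplies effect data without coverage. Adjustment cannot estimate an effect in a combination with no women. The generalisability sentences in the Abstract and at the end of the Discussion do not carry the caveat, and the objectives present the clinics as comparators for programme impact.

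**Conclusion.** The concern holds as a limit on what may be concluded. The effect without coverage, and any change in effect with coverage, have no direct estimate in this design. That follows from the clinic descriptions alone and needs no assumption about rates.

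The non-programme part of a CHUS-intervention-versus-uncovered-clinic difference has no supportable figure. A reader might infer that such a contrast must flatter the programme, but the documents do not give the usual-care rate that would settle even its direction. That coverage modifies the effect is plausible from the timing of treatment in the two arms, but it is not shown.

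The randomised contrast, primary outcome and sample size are unaffected. What changes is the reach of the effect, cost-effectiveness and generalisability claims.

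**What to change.** 1. In the fourth limitation, replace the clause on comparison with uncovered provinces by wording such as: *The programme effect is estimated only under public coverage. Comparison with clinics that do not offer the programme describes usual care by coverage status. Whether the effect carries over to uncovered settings is left to a future multicentre randomised trial.*
2. Qualify the generalisability sentences in the Abstract and in the last paragraph of the Discussion to match.
3. Base programme-effect and cost-effectiveness conclusions on the randomised CHUS contrast. Do not report CHUS intervention minus an uncovered clinic as a programme effect.
4. When presenting the external clinics, show the CHUS control arm and Montreal beside Toronto and Edmonton, and label the comparison as one of usual care.

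Reweighting the randomised result to the case mix of the uncovered clinics is not a substitute. It would align measured patient characteristics and leave coverage untouched.

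The cost is a change of wording and presentation, with no new data or design change. The price is a weaker claim about transferability.
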